### Variables

For the general programme group, enrolment measurements will be height in metres and weight in kilograms (kg), and they will complete a Māori scale of health and well-being, Hua oranga, electronically. Their weight in kg will be recorded at six and 12 months, and at conclusion at 24 months, they will repeat Hua oranga and have a final weight taken. The primary outcome will be changes in weight, and the secondary outcome will be changes in Hua oranga scores. Note that first measurement is at enrolment in the evaluation and many participants at this stage will have been in the BBM programme for a period of time already. At enrolment, their self-reported heaviest weight, and weight at their first BBM visit will be recorded.

For the FTC group, in addition to the data collected above, clinical data from their health records will be sought. This includes diagnosis classifications, past history and current problems of any chronic diseases, especially type 2 diabetes, hypertension, gout, dyslipidaemia, cardiovascular disease, stroke, renal dysfunction, liver disease, osteoarthritis, gall bladder disease, chronic obstructive respiratory disease, and obstructive sleep apnoea. Blood and urine analyses laboratory results, prescribed medications, and other referral letters and discharge summaries will also be accessed. Their blood pressure at enrolment and at 12-weeks will also be recorded.

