### Aim and objectives

The aim of this study is to evaluate the effectiveness of BBM for sustained health and wellbeing outcomes among its predominantly Pacific and Māori participants. The primary hypothesis is that BBM will create valuable, average sustained weight loss (≥ 5% of baseline weight) for participants over three years. Secondary hypotheses include that programme participation will result in improved quality of life (measured in Hua Oranga); and for the FTC cohort, improved cardiovascular and metabolic health outcomes (measured via medical records).

There are two research questions. The first is, how effective are BBM’s general programmes in providing sustained weight loss of ≥ 5% of baseline body weight and improved quality of life measures for its members? The objective is to carry out an impact assessment of BBM’s general programme effectiveness, to estimate the medium to long-term (one to two year) weight loss maintenance and the impact on quality of life of BBM members.

The second question is how effective is BBM’s FTC programme for achieving sustained clinically significant benefits for members who typically experience of Class 3 or 4 obesity [10]? The objective here is an outcome assessment of the FTC programme’s effectiveness, to examine the medium to long-term clinical impact on a sub-cohort (n ~ 50) of members who enter BBM with Class 3 and 4 obesity, body mass index (BMI) > 35 kg/m^2^. As secondary outcomes, we will collect laboratory and clinical data from medical records held by primary care providers. Data collection will occur on three occasions, at commencement of the FTC programme, one and two years later.

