### Statistical analysis

All statistical analysis will be done in R [13] using the lme4 package [14]. The primary outcome of interest is sustained weight loss. How successful BBM is at helping participants lose and maintain 5% weight loss will be a critical outcome measure, however, the effectiveness of BBM compared to other counterfactuals will also be assessed.

The general programme cohort will include existing and new entrants. For existing members we will also have self-reported weights at their first BBM session, which will be considered the baseline or ‘time zero (T0)’ weight with subsequent times measured from then. For example, for a person who started at BBM seven months before enrolment in the study, their reported weight at BBM entry will be T0, their enrolment weight (measured by the research team at study enrolment) will be T7, their 6-month weight will be T13, 24-month weight will be T31. Typically, the pattern of weight loss with weight loss programmes is tick-shaped with a weight loss nadir at 6–12 months followed slow return back towards T0 weight or beyond. Estimated duration of the study will be 24 months of follow-up from enrolment.

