### Analysis of hua oranga scores

The hua oranga scores will be analysed with a general or generalised linear mixed model with proper distribution (gaussian, binomial or poisson) depending on the characteristics of the distribution of the outcomes. The random term is the person (participant). The scores per domain will be analysed as well as the sum of all the scores. Because we have pre- and post-data, all analyses will be followed with a DID analysis to obtain the corrected differences.

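### For existing BBM members the Hua Oranga change starts at study enrolment, not at joining, so the pooled pre-post change does not estimate the effect of participation

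*Protocol article*

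**What the plan says.** Under Aim and objectives, the protocol article states: "Secondary hypotheses include that programme participation will result in improved quality of life". The reference point of that hypothesis is entry to the programme.

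The Variables section sets the timing. At study enrolment, general members are weighed and "they will complete a Māori scale of health and well-being, Hua oranga, electronically"; then "at conclusion at 24 months, they will repeat Hua oranga and have a final weight taken". The same section adds: "Note that first measurement is at enrolment in the evaluation and many participants at this stage will have been in the BBM programme", for some time. Under Statistical analysis: "The general programme cohort will include existing and new entrants".

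For weight, that section repairs the timing: "For existing members we will also have self-reported weights at their first BBM session, which will be considered the baseline", and later times are counted from there. Nothing comparable is described for Hua Oranga. The section on the analysis of Hua Oranga scores names a mixed model with person as the random term. It then justifies a difference-in-difference step with the words "Because we have pre- and post-data".

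Two further facts matter. Under Data collection, the enrolment survey records how long ago each participant joined BBM. Under Participant recruitment, From the Couch (FTC) participants are invited when they register for a programme, and the only exclusion is repeat attenders already in the study.

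**The concern.** The hypothesis concerns what happens to quality of life from joining onward. For a member who joined before study enrolment, any improvement in the first months is already in the first Hua Oranga score. The difference between that score and the one at 24 months describes what happened later: further gain, maintenance or loss.

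Pooling such members with new entrants gives an average of two different quantities, weighted by a mix that recruitment happens to produce. A small or null pooled change could be read as no quality-of-life benefit from BBM when, for many participants, the early part of the benefit was never observed. Weight and Hua Oranga results for the same person would also be reported side by side with different starting points.

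**Working it through.** The protocol gives no expected change, standard deviation or sample size for Hua Oranga, so there is no figure to reproduce. The check has three parts.

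**1. The two outcomes for one person.** Statistical analysis gives the example of a member who joined seven months before enrolment.

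| | Start of measured change | End | Period covered |
|---|---|---|---|
| Weight | T0 (self-reported at first session) | T31 | 31 months since joining |
| Hua Oranga | T7 (study enrolment) | T31 | 24 months; the first 7 are unobserved |

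For a new entrant the two starting points coincide.

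**2. Effect on the pooled change (illustration).** Let s be the share of general members already in BBM at enrolment. Let f be the part of their net gain from joining to final follow-up that was reached before enrolment. Both are assumptions; the protocol says only that such members are many. Suppose new and existing members have the same true net gain since joining. Then

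measured change / true change = (1 − s) + s(1 − f) = 1 − s·f.

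| s | f = 0.25 | f = 0.5 | f = 1 | f = 1.5 |
|---|---|---|---|---|
| 0.25 | 0.94 | 0.88 | 0.75 | 0.63 |
| 0.50 | 0.88 | 0.75 | 0.50 | 0.25 |
| 0.75 | 0.81 | 0.63 | 0.25 | −0.13 |
| 0.90 | 0.78 | 0.55 | 0.10 | −0.35 |

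Here f = 1 means that the whole gain came before enrolment and was kept. A low f means that gains build late, and then little is lost. A value of f above 1 means that part of an early gain fades after enrolment, and the sign can then reverse.

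**3. A fading time course.** The only time course the protocol describes is for weight: a best point at 6 to 12 months, then a slow return. Purely as an assumption, suppose Hua Oranga follows that shape, with a linear rise to a peak of 1 at 9 months and a linear fall to a retained fraction r at 33 months. For the member who joined 7 months earlier:

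- value at enrolment = 7/9 = 0.78
- value at 31 months = 1 − (1 − r)(31 − 9)/(33 − 9) = 1 − 0.917(1 − r)

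| r | Gain since joining | Measured change (enrolment to 24 months) |
|---|---|---|
| 0.5 | +0.54 | 0.54 − 0.78 = −0.24 |
| 0.75 | +0.77 | 0.77 − 0.78 = −0.01 |
| 1.0 | +1.00 | 1.00 − 0.78 = +0.22 |

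A new entrant, measured from zero, shows the full gain since joining in each case.

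**The case against.** The protocol is open about the timing. A past wellbeing score cannot be recovered in the way a remembered entry weight can, so different starting points partly follow from what data can exist. The Hua Oranga section lists no fixed effects at all; a full list is commonly left to a statistical analysis plan, and none is shown here. The missing new-versus-existing term is therefore not an error in itself. This stands. What remains is that the article states a participation hypothesis and calls the scores pre and post data, while its own account of timing says otherwise for existing members.

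A reader might infer that Hua Oranga cannot measure the effect of participation at all. The documents do not support that. New general entrants have a score at or near entry, as do FTC registrants, although some of the latter may have had earlier BBM exposure. Time since joining is recorded, so the groups can be separated. The lack of a control group limits any causal reading, but that is a different matter.

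A reader might also infer that the change is certainly diluted toward zero, or put a percentage on the loss, such as 20 to 50% of the gain remaining if 50 to 80% are existing members. That requires an assumed share and an exact plateau after enrolment, and the protocol gives neither.

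**Conclusion.** The concern holds for general members who joined before study enrolment. Their Hua Oranga change runs from enrolment to 24 months, with no entry value to stand in as time zero, so it does not answer the participation hypothesis. Pooled with new entrants and FTC enrolees, it biases the estimate of the participation effect. The likely direction is toward no benefit, provided that early gains are kept. Fading gains could turn the measured change negative despite a net gain since joining, and late gains would leave little bias.

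The size cannot be computed from the protocol. The ratios above, from 0.94 down to −0.35, show only how far the answer depends on two unstated quantities. The outcome is secondary and the weight analysis is not touched, but the Hua Oranga conclusion is exposed and the remedy is within reach.

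**What to change.** In the Hua Oranga model, add an entry-group (new versus existing) by time term, or a months-since-joining by time term, using the time since joining already collected. Base the conclusion on the participation hypothesis on the estimate for people at or near programme entry: new general entrants, and FTC enrolees without earlier BBM exposure. Report the change in existing members separately, as maintenance of quality of life, and say in the text that Hua Oranga and weight have different starting points for them.

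No new data are needed. The cost is precision. With the target of 1000 general members, the new entrants number 1000(1 − s): 500 at s = 0.5, 250 at s = 0.75, 100 at s = 0.9. With equal spread and before dropout, the standard error of their mean change exceeds that of the pooled change by a factor of 1/√(1 − s), that is 1.41, 2.00 and 3.16. The months-since-joining version keeps everyone in the model, but its estimate at zero months depends on the assumed shape of that relation. Basing the conclusion on near-entry participants is a choice about the question asked; existing members stay in the model and in the report.

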### Data collection

Pacific research assistants will undergo training in recruitment and data collection and be provided with detailed step-by-step instructions. They will contact respondents to arrange a time and location to review the Participant Information Sheet (PIS) and gain consent, preferably at a BBM exercise centre. If requested, the PIS and consent form can be provided in te reo (Māori language), Samoan and Tongan. A log of all attempted communications with potential participants will be maintained. Once participants have consented, they will be invited to complete the online survey, which includes length of time since first joining BBM, weight at that time, frequency of attendance at BBM exercise sessions in the last three months, the Hua Oranga survey and demographic details (such as age, gender, ethnicity).

All participants will have their height and weight measured at enrolment by BBM staff and research assistants who will have undergone training using standardised protocols [11]. Participants will be weighed using Seca Scale Column Model 703 300 kg scales without footwear and light clothing only. Height is measured using the study’s stadiometer without shoes. Participants’ retrospective self-recorded weights, for example when they first entered the BBM programme, will also be collected.

Additional data will be collected for FTC participants. BBM trainers already measure and record blood pressure in this group, using an extra-large cuff calibrated sphygmomanometer. All FTC participants will be asked to consent to accessing their National Health Identification number and/or details of their primary healthcare provider / general practitioner to enable extraction of clinical details from their medical records: chronic disease diagnoses, diagnostic laboratory results and reports, clinic letters, e-referrals, prescribed medications, hospital appointments and admissions, and discharge summaries. Most New Zealand patients are enrolled in a Primary Health Organisation (PHO) through their registered general practice. PHOs collect primary care data from their member practices [12]. There are eight geographically dispersed and overlapping PHOs in the Auckland region. It is anticipated that most FTC participants will be enrolled with the three largest PHOs operating in South Auckland (where most BBM members live). Patient data will be extracted by these organisations on application using their data management processes. Where participants attend practices that belong to other PHOs, the clinical data will be sought via direct contact with individual practices.

Routine data for FTC participants collected by BBM will be included in the analyses. These data include age, frequency of exercise per week, whether they suffer from a respiratory condition or asthma, high blood pressure, blood disorder, diabetes, arthritis, epilepsy of seizures, past history of stroke, and whether they have been pregnant, had major surgery or hospitalised in the previous 12 months.

### Statistical analysis

All statistical analysis will be done in R [13] using the lme4 package [14]. The primary outcome of interest is sustained weight loss. How successful BBM is at helping participants lose and maintain 5% weight loss will be a critical outcome measure, however, the effectiveness of BBM compared to other counterfactuals will also be assessed.

The general programme cohort will include existing and new entrants. For existing members we will also have self-reported weights at their first BBM session, which will be considered the baseline or ‘time zero (T0)’ weight with subsequent times measured from then. For example, for a person who started at BBM seven months before enrolment in the study, their reported weight at BBM entry will be T0, their enrolment weight (measured by the research team at study enrolment) will be T7, their 6-month weight will be T13, 24-month weight will be T31. Typically, the pattern of weight loss with weight loss programmes is tick-shaped with a weight loss nadir at 6–12 months followed slow return back towards T0 weight or beyond. Estimated duration of the study will be 24 months of follow-up from enrolment.

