## Methods/design

### Study design

This is a quasi-experimental quantitative cohort study design. The general programmes participants will have pre-measurements (measured or self-reported weight at entry to BBM) and multiple post-measurements (measured weight at various intervals), and the FTC participants will have pre-post programme weight measurements. Evidence from the literature of the natural course of weight change in populations like the BBM participants with and without interventions will enable counterfactual comparisons. This study follows the Strengthening the Reporting of Observational Studies in Epidemiology (STROBE) Statement and a Standard Protocol Items: Recommendations for Intervention Trials (SPIRIT) checklist has been completed.

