### Participant recruitment

For the general programme, participants will be recruited through study advertisements on BBM’s social media platforms, and as posters in physical locations (the exercise centres). BBM trainers will promote the study to BBM attendees. All attendees over the age of 16 years will be eligible to participate.

For FTC group participants, all people registering for three 12-week programmes will be invited to enrol in the study. All FTC participants will be eligible, with the exclusion of repeat attenders already enrolled in the study.

Participants from both the general and FTC groups will be offered a koha (gift) of a $40 token at the 24-month follow-up. Participants will continue to be enrolled until the target samples are reached. Given recurrent lockdowns and restrictions on class sizes due to COVID-19, it is anticipated that the study will be extended by one year to enable 24 month follow-up of all participants.

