## Discussion

It is important to note that the fundamental question for both our study groups is whether weight loss can be maintained over the long haul. Multiple studies have shown that many diet and physical activity programmes can create short-term weight loss. Similarly, many studies have shown that the loss and maintenance of weight can have important health benefits. The critical remaining questions are implementation-related: How many people can be attracted to a programme (especially from communities with high obesity prevalence), how many can stay with the programme (duration of engagement is closely related to weight loss maintenance), and what are the long-term weight loss results?

If this study demonstrates robust empirical evidence of programme success, this could shift the paradigm for achieving the ultimate public health objective of sustained weight loss in an era of high sedentariness and energy-dense food environment. This paradigm switch, especially for communities with a collectivist culture, may result in a move from the one-on-one advice of expert professionals in a clinic environment, to a many-on-many participation with non-experts in community settings. Internationally, it is the collectivist cultures of indigenous and migrant and minority populations, living within dominant individualist western ideologies, which have much greater burdens of obesity [37]. If a robust and culturally informed evaluation of BBM demonstrates the effective features of this community-based approach to sustained weight loss, this could be of high relevance and benefit to other indigenous and migrant populations. In Aotearoa, achieving equity for Pacific and Māori engagement in health enhancing programmes remains an important strategy for achieving better health and wellbeing outcomes, and quality of life for whānau (family).

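### Existing members' baseline is a retrospective self-report, and their change up to enrolment is conditional on still attending; the plan pools this with new entrants' change on one time axis

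*Protocol article*

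**What the plan says.** The Statistical analysis section of the protocol article states "The general programme cohort will include existing and new entrants" and defines time zero for the former: "For existing members we will also have self-reported weights at their first BBM session, which will be considered the baseline". Later times count from that session. In its example, a member who joined seven months before enrolment has enrolment at T7 and later visits at T13 and T31.

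Other sections show where this baseline comes from. Study design describes the pre-measurement as "measured or self-reported weight at entry to BBM". Data collection has the survey completed after consent ask for "length of time since first joining BBM, weight at that time". Variables adds "Note that first measurement is at enrolment in the evaluation", and that "many participants at this stage will have been in the BBM programme for a period of time already".

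On who can enter, Setting names attendees of the Auckland programmes from 2021, and Participant recruitment says "All attendees over the age of 16 years will be eligible to participate". The Background dates BBM to 2014.

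The analysis text after the figures specifies a linear mixed model with person as the random and time as the fixed variable. It then compares the result with the literature curve at chosen times. Success is a mean sustained loss of at least 5% of baseline weight (Aim and objectives).

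**The concern.** For an existing member, the interval from T0 to enrolment differs from every later interval in two ways.

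First, it is observed only in people who are attendees when the study recruits. Someone who joined at the same time and stopped before 2021 is outside the sampling frame. The Discussion itself says that "duration of engagement is closely related to weight loss maintenance", so the condition for being observed is tied to the outcome.

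Second, the instrument changes from self-report to a scale over that same interval, so any systematic reporting error appears as weight change.

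The plan gives this interval the same standing as change measured after enrolment, pools it with new entrants, and compares the result with a 5% target and with published trajectories. A mixed model can use incomplete records from enrolled people, but it has no records at all from joiners who left before enrolment. A larger sample narrows the interval around a shifted estimate.

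**Working it through.** **The plan's own time clock.** 7 + 6 = 13 and 7 + 24 = 31, as the article states. Measured from enrolment, the same visits fall at 0, 6 and 24 months, and the unmeasured pre-enrolment segment drops out.

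**Size of the shift.** The documents give no standard deviation, retention, reporting error or share of existing members, so all of these are assumptions. True mean change is set to zero and results are percentages of baseline weight.

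- Selection shift = ρ × SD × φ(c)/p, where p is the fraction of joiners still attending, c = z(1−p), SD is that of percentage weight change, and ρ is the correlation between loss and staying.
- Reporting shift = r/(1+r), where r is the over-statement of first-session weight (negative for under-statement).
- Cohort shift = f × (selection + reporting), where f is the share of existing members.

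φ(c)/p is 0.798 at p = 0.5 and 1.159 at p = 0.3.

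| Scenario | Selection | Reporting | Existing members | Cohort, f = 0.5 | Cohort, f = 0.9 |
|---|---|---|---|---|---|
| Low: SD 4, ρ 0.1, p 0.5, r 0 | 0.1 × 4 × 0.798 = 0.32 | 0 | 0.32 | 0.16 | 0.29 |
| Middle: SD 6, ρ 0.2, p 0.3, r +1% | 0.2 × 6 × 1.159 = 1.39 | 0.99 | 2.38 | 1.19 | 2.14 |
| High: SD 8, ρ 0.3, p 0.3, r +2% | 0.3 × 8 × 1.159 = 2.78 | 1.96 | 4.74 | 2.37 | 4.27 |
| Offset: SD 6, ρ 0.2, p 0.3, r −2% | 1.39 | −2.04 | −0.65 | −0.33 | −0.59 |

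Against the 5% target, the first three rows are 6%, 48% and 95% among existing members, and 3%, 24% and 47% at f = 0.5. These are scenarios, not bounds.

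**Against sampling error.** With the target of 1000 and an assumed SD of 6%, the standard error of a mean change is 6/√1000 = 0.19 percentage points. A shift of 1 to 2 points would be several times that.

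**Where on the time axis it acts.** An existing member with m months' prior attendance supplies T0, then nothing until m, then m + 6, m + 12 and m + 24. Observed weights at early post-baseline times therefore come from new entrants and recent joiners. The literature follow-up is 3 to 24 months. A member with m above 24 has no follow-up weight inside that window, so bias in that comparison comes mainly from members with up to about 24 months' prior attendance. Times clearly beyond 24 months come from existing members alone, because follow-up is 24 months from enrolment; new entrants do not dilute the bias there.

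**The case against.** The strongest reply has four parts.

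*Direction.* The Discussion's remark on engagement is as consistent with staying causing maintenance as with successful people choosing to stay. That stands: the documents do not show how much of the association is selection. On either reading, though, the pre-enrolment change describes those who stayed, not those who joined.

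*Who is recruited.* Social media advertising may reach lapsed members, and the article calls the earlier weights self-reported or self-recorded, so some may be contemporaneous records. Both points soften the concern. Neither removes it: eligibility is worded for attendees, and no rule separates recorded from remembered weights.

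*Time axis.* A reader might infer that late times such as T31 come only from long-stay survivors. The article's own T31 case had attended for seven months at enrolment, and nothing makes later weighing depend on continued attendance. The selection is on attending at enrolment.

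*No-change counterfactual.* The Discussion argues that no weight change is a plausible course without intervention. That concerns what would happen without BBM. It does not address whether the change attributed to BBM is distorted by who is observed and how the baseline was obtained.

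An unseen analysis plan might add analyses by tenure. The article nevertheless fixes the baseline and the pooling, and those are what is at issue.

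**Conclusion.** The point holds as a flaw in a stated rule for the primary outcome. For existing members, baseline is a retrospective self-report, change up to enrolment is conditional on attendance, and the planned model cannot correct for joiners who left.

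The size is not established. The assumed scenarios give about 0.3% to 4.7% spurious loss among existing members and about 0.2% to 2.4% in the cohort if half are existing members. A reader might infer that the bias by itself would produce much of the 5% target. The documents do not support that: every input is assumed, the share of existing members is unstated beyond being many, and a 2% under-statement of entry weight turns the middle scenario's selection shift into −0.65%. Selection favours the programme only if people who lose weight are likelier to stay, and reporting error has no known sign. Confidence is high in the mechanism and low in any single figure.

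**What to change.** State in the protocol and analysis plan that:

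- the from-joining estimate, and the comparison with the literature curve, use new entrants enrolled within a short, fixed window of their first session;
- existing members' change from measured enrolment weight is reported separately as a maintenance estimate;
- the mixed model includes an entry-group (new/existing) by time term;
- existing members' trajectory from self-reported T0 is kept as a descriptive secondary result, labelled as conditional on attendance at enrolment.

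No new data are needed: measured enrolment weight and time since joining are already to be collected. The cost is fewer people and a wider interval for the from-joining estimate. That loss could be material, since many participants will be existing members and lockdowns have already delayed recruitment. The from-joining result would also describe new entrants rather than the whole membership, which is why the maintenance estimate should be reported beside it.
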